### Assignment of Interventions

Block randomization will be used to help maintain balance in allocation at each site. Randomization assignments will be computer generated and allocated via an electronic data capture system. Randomization is 1:1 to either the 10‐kHz SCS + CMM group or the CMM group. Figure 2 shows the study flow for both randomized groups, and Table S1 shows the timing of assessments.

**Figure 2 papr12945-fig-0002:**
[figure not shown]
Protocol flow. CMM, conventional medical management; HF10, high‐frequency stimulation at 10 kHz.

### 10‐kHz SCS + CMM Group

Subjects randomized to 10‐kHz SCS + CMM will undergo a 14‐day SCS trial phase. Two percutaneous leads with 8 contacts each will be placed in the epidural space spanning vertebral levels T8 to T11.^13^ Stimulation at a frequency of 10 kHz and pulse width of 30 µicroseconds will be delivered from an external pulse generator. The stimulation target and current amplitude will be adjusted until at least 50% self‐reported back pain reduction from baseline is achieved, defined as trial success, or until conclusion of the trial phase. Subjects who pass the trial phase will be scheduled for permanent implantation of the 10‐kHz SCS system (Senza, Nevro Corp., Redwood City, CA, U.S.A.) with investigator and subject agreement. Subjects who fail the trial phase will have leads explanted and will not receive a permanent SCS system but will be followed‐up for 6 months.

The permanent device implantation procedure will be per the manufacturer’s physician implant manual and standard of care. The leads will be placed trans‐fascially and anchored to the fascia, and will be tunneled to a subcutaneous pocket where the implantable pulse generator (IPG) is housed. The IPG is typically implanted in the lower back/buttock region. The device will be activated 0 to 14 days following permanent implantation. The subject will be instructed on the use of the IPG charger and remote control. Programming adjustments will be made at scheduled follow‐ups as needed.

### Conventional Medical Management

All subjects will continue with their CMM, defined as the best standard of care for each individual patient, as determined by the investigator. Table 3 provides examples of therapies that could be part of the investigators’ CMM, but other treatments are not excluded. Previously beneficial treatments may be continued. Conservative care should have been rendered that was generally consistent with the American College of Physicians and the American Pain Society Guidelines as published in the *Annals of Internal Medicine*
^34^ and an interventional pain management guideline from the American Society of Interventional Pain Physicians.^35^

**Table 3 papr12945-tbl-0003:** Conventional Medical Management Exemplary List

Oral medications (including analgesic medication, nonsteroidal anti‐inflammatory drugs, neuromodulating agents, antidepressants) Topical analgesics, compound creams, or counter‐irritants Combined physical and psychological management Physical therapy Back rehabilitation program Spinal manipulation and spinal mobilization Traction Acupuncture/acupressure Cognitive behavioral therapy Nerve blocks Epidural steroid injections Transcutaneous electrical nerve stimulation

### Crossover

Subjects randomized to either treatment group are eligible to cross over to the alternative treatment arm at the 6‐month visit if they meet all the following criteria:
<50% back pain relief from baselineDocumented subject dissatisfaction with the treatmentInvestigator agreement with crossover

In the case of a crossover from 10‐kHz SCS + CMM to CMM, the SCS therapy will be switched off and the subject will continue with CMM treatment through the 12‐month visit. If a subject randomized to CMM crosses over to 10‐kHz SCS + CMM, he or she will then undergo a trial and implantation as shown in Figure 2.

### Safety Considerations

The Senza system (including any approved system or component models) is to be used in accordance with its U.S. Food and Drug Administration–approved labeling; therefore, a safety monitoring committee is not required. Adverse events will be assessed at all follow‐ups and any unscheduled visits, and all treatment‐related and serious adverse events will be recorded.

The safety endpoints will be the types and incidence of related adverse events and neurological assessments in each group. All serious adverse events will be reviewed by the principal investigator at each site as they occur and reported in accordance with Medical Device Reporting requirements of 21 CFR 803 when using commercial medical devices.

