### Project Management

The study recruitment will be done by investigators and site research coordinators, from patients currently being treated at the site, or referred from primary care, spine surgeons, or other spine care specialties. The principal investigators will verify eligibility and be responsible for conducting the study based on the clinical investigation plan and good clinical practice. Investigators will obtain consent, perform the trial and implantation procedures, perform the neural assessments, and rate the severity of adverse events. Research coordinators will obtain consent, collect study data, and administer questionnaires. Nevro field clinical engineers will provide device support and optimize programming as directed by the investigators.

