## Discussion

### Theory

The primary endpoint is pain intensity at 3 months using the gold standard of patient report on a VAS,^30^ which is required for labeling claims.^38^ The response definition of at least 50% pain relief permits comparison with other studies and demonstrates separation from placebo, which has been estimated at approximately 30%.^30^, ^39^ The secondary endpoints are at 6 months and include measures of function that are recommended for chronic pain trials.^30^

The safety analysis for this study will include study‐related adverse events, as well as explantations for any cause. Explantations are important to report because they represent additional surgical procedures the patients must undergo, and they represent additional costs to the therapeutic system. Explantation rates have been reported by Stauss et al.^40^ and Van Buyten,^25^ both retrospective analyses, with explantation rates due to loss of efficacy ranging from 1.2% to 5.0%. Although not identified as explantations for the purpose of their analysis, in the Van Buyten article, the rate of explantation due to battery depletion in the nonrechargeable cohort was reported as 37.4% (173/462) within the mean observation period of 2.24 years.

The clinical effect measurement is strengthened by including multiple sites and investigators who are both spine surgeons and pain management specialists, providing a real‐world dataset. The requirement of a surgery consult provides verification of the subject’s surgical candidacy and record of pain etiology.

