### Limitations

Due to the nature of the treatment groups, it is not feasible to blind either the subjects or the clinical site personnel to treatment group assignment. Subjects randomized to 10‐kHz SCS + CMM will receive stimulation delivered through an implanted SCS system. The system requires the use of external components for programming and daily recharging, thus precluding subjects from being blinded to their treatment group.

The lack of blinding provides a potential for bias. In preparing the investigational plan, elements have been put in place to anticipate and minimize potential sources of bias.
The qualifications of each investigator and his or her ability to appropriately screen and treat subjects and to comply with investigational plan requirements will be reviewed before their participation in the trial.The study will be conducted under a common protocol at all study sites.The sponsor, investigators, and study participants will remain blinded to aggregated study results, except for recommendations made during a single, preplanned interim analysis.In order to minimize potential assessment bias, the subjects will receive standard instructions for completing the questionnaires.

One limitation of this study is the potential for a “nocebo effect,” since one arm of this study entails the continuation of the CMM treatment the patients have been receiving. But this effect is mitigated due to the regular care and assessment that the CMM arm group receives within the study. It is likely that some patients will achieve improved treatment results compared to previous CMM in this more intensive care scenario.

In addition, this pragmatic open‐label study is not designed to remove the effect of a subject’s expectations for the therapy or placebo effect. In the practice of real‐world chronic pain treatment, the placebo effect may be considered part of the therapy, “shaping the central nervous system toward pain relief,” since psychological factors are known to influence chronic pain management.^42^

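### The adverse-event part of the safety endpoint is limited to related events in an open-label trial, and no all-cause serious-event incidence by randomized arm is specified

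*Protocol article*

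**What the plan says.** Three places in the protocol article bear on this.

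- **Methods, Safety Considerations.** On recording, "all treatment‐related and serious adverse events will be recorded". On handling, "All serious adverse events will be reviewed by the principal investigator at each site as they occur", followed by device reporting. On the endpoint, "The safety endpoints will be the types and incidence of related adverse events and neurological assessments in each group". The section also says that "therefore, a safety monitoring committee is not required", because the device is used within its approved labeling.
- **Discussion, Theory.** The safety analysis is described as covering study-related adverse events "as well as explantations for any cause".
- **Discussion, Limitations.** The trial is open label: "it is not feasible to blind either the subjects or the clinical site personnel to treatment group assignment".

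Project Management says that investigators "perform the neural assessments, and rate the severity of adverse events". Neither that section nor any other says who judges relatedness.

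**The concern.** The trial adds a lead trial, an implant and stimulation to usual care. A reader deciding whether to offer this wants to know whether subjects randomized to it had more or fewer serious events, whatever their cause. That comparison is protected by randomization. A count filtered by relatedness is not, for two reasons.

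First, the filter is a judgment. Site personnel know the arm, and no independent or blinded judge is named.

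Second, the filter selects different things in the two arms. Under 10-kHz SCS + CMM, an event can be related to the procedure, the device or the CMM. Under CMM alone, it can be related only to the CMM, which is largely a continuation of earlier care. The endpoint is to be reported in each group, so readers will set the two incidences side by side even though no test is specified.

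**Working it through.** The article states no adverse-event rate and no safety sample size, so there is no safety figure to reproduce. The check is a comparison of the passages, followed by an illustration on assumed values.

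**1. What each place covers.**

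| Place | Adverse events covered | Relatedness filter | Other items |
|---|---|---|---|
| Safety Considerations, recording rule | Treatment-related events; serious events | *Treatment-related* for non-serious events; none for serious events | – |
| Safety Considerations, handling | Serious events | None | Site review, device reporting |
| Safety Considerations, endpoint | Related events | *Related* | Neurological assessments |
| Theory | Study-related events | *Study-related* | Explantations for any cause |
| Table 5, healthcare utilization | Not an adverse-event outcome | None | Emergency visits and admissions compared between groups |

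Serious events of any cause are recorded and reviewed. No row makes their incidence by randomized arm a safety outcome. The two rows that define the safety outcome (endpoint and Theory) both apply a relatedness filter.

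**2. What could be done with existing data.** Serious events are recorded whatever their cause, so an all-cause serious-event incidence needs nothing new. Unrelated non-serious events are not recorded, so an all-cause count of *all* adverse events would need wider recording. That is not proposed here.

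**3. How attribution moves the count.** Let *r* be the true risk of a serious event, equal in both arms. Let *s* and *c* be the shares of events called related in the SCS and CMM arms. The related-only incidence is *r* × *s* against *r* × *c*. The all-cause incidence is *r* against *r*. All values are assumptions.

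| *r* | *s* | *c* | Related, SCS | Related, CMM | All-cause, both arms |
|---|---|---|---|---|---|
| 5% | 0.5 | 0.1 | 2.5% | 0.5% | 5% |
| 5% | 0.5 | 0.3 | 2.5% | 1.5% | 5% |
| 5% | 0.7 | 0.1 | 3.5% | 0.5% | 5% |
| 10% | 0.5 | 0.1 | 5.0% | 1.0% | 10% |
| 10% | 0.5 | 0.3 | 5.0% | 3.0% | 10% |
| 10% | 0.7 | 0.1 | 7.0% | 1.0% | 10% |

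By construction the whole contrast comes from the shares. Interchanging *s* and *c* reverses its direction: with *r* = 5%, *s* = 0.1 and *c* = 0.5, it reads 0.5% against 2.5%. The table covers only serious events. The endpoint as written also includes non-serious related events, so these are not predictions of what it would show.

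**4. Time window.** The Crossover section lets CMM subjects proceed to a trial and implant from the 6-month visit. The footnote to Table 5 restricts the 12-month observational outcomes to within-group analysis for this reason. A comparison by randomized arm is therefore cleanest up to that point.

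**The case against.** The strongest reply is that the safety plan is broader than one word suggests, and much of it stands.

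- A reader might infer that the endpoint counts nothing but related events, or that no attribution-free comparison between arms exists. The documents do not support either. The endpoint sentence includes neurological assessments in each group, which need no causal judgment. Table 5 compares emergency visits and hospital admissions between groups. However, the first does not capture serious events in general, and the second is a utilization outcome.
- A reader might infer that unrelated serious events are discarded. They are not: they are recorded, reviewed and reported. The statistical section promises descriptive summaries of outcome data, and the Theory wording is not exhaustive.
- A reader might take it as stated that unblinded investigators decide relatedness. That is plausible, but the article gives them only the severity rating. What can be said is that no independent or blinded judge is named.
- Related events are possible under CMM. Table 3 lists oral medications, nerve blocks and epidural steroid injections. The arms differ in what an event can be related to; the control arm is not empty.
- Explantations appear in Theory but not in the endpoint sentence. This is a mismatch to align, not a contradiction. Nothing shows that the three relatedness terms select different events.

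It can also be said that a table of serious events by arm is routine detail for the full protocol or analysis plan. That would answer a silence. Here the article states the endpoint and limits its adverse-event part to related events, so the wording itself is open to comment.

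**Conclusion.** The point holds in a limited form. The adverse-event component of the safety endpoint is restricted to related events although all serious events are recorded. As a result, no all-cause serious-event incidence by randomized arm is specified, and the related-only incidence depends on attribution in an open-label trial.

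The size is unknown because no event rate is given. The illustration shows only that equal true risks can look unequal, in either direction. The conclusion rests on reading the recording rule as covering serious events of any cause, which the separate sentence on review of all serious events supports.

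The matter touches no primary or secondary efficacy endpoint. It is a worthwhile and inexpensive improvement to the safety reporting, not a defect that undermines the trial.

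**What to change.** Revise the endpoint definition in Safety Considerations as follows:

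1. Add the incidence of all serious adverse events regardless of relatedness, by randomized arm, up to the 6-month crossover point. Describe later events separately by treatment received.
2. Keep related adverse events as a within-arm description, split into device-, procedure- and CMM-related.
3. Keep the neurological assessments.
4. List explantation for any cause, so that the section matches Theory.
5. Use one term for relatedness throughout.

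The cost is a wording change and one extra table. Serious events are already recorded and explantations are already planned for analysis, so no new data collection is needed, and the change remains possible with enrollment closed.

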### Follow‐up

Assessments will be performed at 1, 6, 9, and 12 months for both groups (see Table S1). Unscheduled visits may occur at any time during the study for the assessment of possible adverse events, medication changes, and programming adjustments.

### Data Management and Statistical Analysis

Descriptive statistics will be used to summarize all subject baseline and outcome data collected during the study. Continuous variables will be summarized using means, standard deviations, and ranges. Categorical variables will be summarized in frequency distributions.

Analysis populations defined for the study include intention‐to‐treat (ITT) and per protocol (PP). The ITT population includes all randomized subjects, while the PP population includes subjects who completed the visit corresponding to the endpoint being analyzed. Note that subjects who fail the temporary trial will be included in the ITT population for the high‐frequency stimulation at 10 kHz (HF10) + CMM arm.

The primary endpoint will be evaluated with a Fisher’s exact test comparing the percentage of subjects in each group who achieve a 50% improvement in their back pain VAS score at the primary efficacy assessment in the ITT population. The following secondary endpoints will be successively evaluated (hierarchical closed test approach) at study completion in the order shown with a 0.05 significance level for difference between groups in the PP population until statistical significance is not achieved.

The comparison between HF10 + CMM and CMM alone in terms of healthcare resource use (HRU) will be made based on doctor’s office visits, emergency room visits, or hospital stays, as well as on medical tests and procedures. Medication use (opioids and medication for CLBP), work status, health status (12‐Item Short Form Survey [SF‐12]), quality of life (EuroQol 5‐Dimension, 5‐Level Instrument [EQ‐5D‐5L]) will be used in the cost‐effectiveness analysis. The change from baseline to 6‐month follow‐up will be compared for CMM vs. HF10 + CMM for all these parameters. In addition, subjects can be used as their own control comparing HRU at baseline to HRU after baseline for the HF10 + CMM arm, or pre‐ and post‐crossover for those crossing over from the CMM to HF10 + CMM at 6 months. Parametric functions (eg, Weibull, Gompertz, etc.) will be used to extrapolate from 6‐month HRU to 1, 2, and 3 years out. HRU will be associated with direct medical costs using fee schedules, Medicare claims, and peer‐reviewed literature. Changes in EQ‐5D‐5L index scores will be used to assess changes in health status and the economic value of the addition of HF10 to CMM.

Observational outcomes will be compared between groups using statistical tests appropriate to the type of outcome.

Additional exploratory analyses may be performed to examine the consistency of results in selected subgroups (eg, based on gender, study site, age, body mass index, mental health [based on Patient Health Questionnaire (PHQ‐9) response], pain duration, pain severity, etc.). These analyses may also take the form of multivariable analyses, where the contributions from membership in multiple subgroups to a study endpoint are simultaneously estimated.

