## Methods

The study is a randomized, controlled, multicenter trial investigating the clinical and cost effectiveness of 10‐kHz SCS for NSRBP when used in addition to CMM.^29^ Up to of 216 patients with NSRBP will be randomized 1:1 to receive either CMM alone or 10‐kHz SCS in addition to CMM (10‐kHz SCS + CMM). The total follow‐up period is 12 months for all participants, with an optional crossover at 6 months. Subjects may be withdrawn from the study for reasons such as entry criteria failure, trial failure, subject or investigator request, lost to follow‐up, subject pregnancy, or adverse event. The study protocol and reporting followed Consolidated Standards of Reporting Trials (CONSORT) guidelines, and the outcomes included were based on the guidelines from the Initiative on Methods, Measurement, and Pain Assessment in Clinical Trials (IMMPACT).^30^ The trial registration number is NCT03680846.

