### Missing Data

Since the primary analysis of the primary study endpoint at 3 months will be in the ITT population, a sensitivity analysis will be performed to examine the impact of any missing data on the observed results. This sensitivity analysis will use the multiple imputation method for estimating missing primary endpoint data, based on available baseline, 1‐month, and 3‐month follow‐up data.

All other analyses of secondary, tertiary, and exploratory analyses will be based on the PP population and available data. In the case of questionnaires with established rules for scoring results in the presence of isolated missing items, those rules will be followed.

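### The five confirmatory secondary endpoints are tested in visit completers rather than as randomized, and the article leaves it unclear whether SCS trial failures are in that set

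*Protocol article*

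**What the plan says.** All places are in the Protocol article.

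- **Data Management and Statistical Analysis** defines two populations. For the first, "The ITT population includes all randomized subjects". The second, PP, is defined only by attendance: "while the PP population includes subjects who completed the visit corresponding to the endpoint being analyzed". No adherence, implantation or trial-success condition is attached to PP.
- The same section adds a note on the SCS arm: "Note that subjects who fail the temporary trial will be included in the ITT population". It does not mention PP.
- It then fixes the set for the ordered secondary tests, "with a 0.05 significance level for difference between groups in the PP population until statistical significance is not achieved". Table 4 lists the five endpoints, all at 6 months: ODI response, percentage change in back pain VAS, PGIC response, EQ-5D-5L and change in opioid use.
- **Missing Data** repeats the choice: "All other analyses of secondary, tertiary, and exploratory analyses will be based on the PP population and available data". The only imputation described is a multiple-imputation sensitivity analysis of the 3-month primary endpoint.
- **10-kHz SCS + CMM Group** says that subjects who fail the temporary trial "will not receive a permanent SCS system but will be followed‐up for 6 months".
- **Methods** (opening paragraph) gives a general withdrawal rule that names trial failure: "Subjects may be withdrawn from the study for reasons such as entry criteria failure, trial failure, subject or investigator request, lost to follow‐up".

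**The concern.** PP is a misleading label here. Membership depends on a post-randomization event, attending a visit, and not on adherence to the protocol. Comparing arms in such a set gives up the protection of randomization, because those who stop attending may differ between arms in ways related to outcome.

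This design gives a specific reason to worry. Only the SCS arm passes through a post-randomization trial phase that identifies subjects with less than 50% relief; the CMM arm has no equivalent step. If trial failures were withdrawn before 6 months, the SCS arm alone would lose subjects identified as poor responders.

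The stakes lie in the secondary claims. Study Goals and Objectives names pain relief, disability, quality of life and opioid use as the measures of clinical efficacy. Of these, only pain relief has an ITT test; the other three are tested only in completers, at a 0.05 level and in a fixed order that presents them as confirmatory. The healthcare-use comparison follows the same rule. Primary and secondary results could then describe different populations.

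**Working it through.** **1. Are trial failures in the PP set?** Setting the statements side by side:

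| Statement | Implication for PP at 6 months |
|---|---|
| PP = completed the visit for that endpoint | A trial failure who attends at 6 months qualifies |
| Trial failures are followed for 6 months | They can attend that visit |
| Withdrawal is permitted for trial failure | A withdrawn subject has no 6-month visit and is out |
| The note keeps trial failures in ITT | Silent on PP |

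The definition does not exclude trial failures. Whether they are present depends on how the withdrawal rule is used, which the article does not say.

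**2. The plan's own figure.** Sample Size Calculation assumes 60% against 36%, 90% power, two-sided 0.05 and Fisher's exact test, giving 98 per group. The continuity-corrected formula returns 98, and exact Fisher power at 98 per group is 90.7%. The figure reproduces.

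**3. Size of a possible distortion.** From the article: 98 per arm, Fisher at two-sided 0.05, and a 36% rate (the control assumption for the primary endpoint, borrowed here for a generic binary secondary endpoint). Assumed: a share f of the SCS arm has no 6-month visit, the missing respond at rate r, CMM loses nobody, and there is no true difference.

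The SCS rate among completers is (0.36 − f·r)/(1 − f), with n = 98(1 − f) rounded:

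- f = 10%, r = 0: 0.36/0.90 = 40.0%, n = 88
- f = 10%, r = 18%: (0.36 − 0.018)/0.90 = 38.0%, n = 88
- f = 20%, r = 0: 0.36/0.80 = 45.0%, n = 78
- f = 20%, r = 18%: (0.36 − 0.036)/0.80 = 40.5%, n = 78

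Exact Fisher rejection rates against 98 CMM subjects at 36%:

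| Share lost, SCS only | Missing respond at arm rate (36%) | At half the arm rate (18%) | None respond |
|---|---|---|---|
| 0% | 3.4% | 3.4% | 3.4% |
| 10% | 4.3% | 5.1% | 7.6% |
| 20% | 4.1% | 8.4% | 21.4% |

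The first column of rates carries no bias. Its small rise above 3.4% reflects the discreteness of Fisher's test with unequal groups. Part of each increase in the other columns has the same source.

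**4. Direction.** If the same non-responders are lost from CMM only, the rejection rates are the same (7.6% and 21.4%) but the spurious difference is −4.0 or −9.0 points, against SCS. If 10% are lost from both arms, all non-responders, both become 40% and there is no bias under the null. At the design rates, however, that equal loss widens 60 − 36 = 24.0 points to 66.7 − 40.0 = 26.7, while loss from SCS only widens it to 66.7 − 36.0 = 30.7.

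**The case against.** The strongest reply is that the article does not drop trial failures. It follows them for the full 6 months, which is when all five secondary endpoints are measured, and PP asks only for attendance. The withdrawal sentence is permissive and part of a general list. This stands. A reader might infer that trial failures disappear from every secondary analysis and that each secondary claim is therefore biased towards SCS; the text supports neither step. Withdrawal on request and loss to follow-up can occur in both arms, and dissatisfied CMM subjects who leave would push the other way.

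It is also fair to say that the higher rejection rates are one-sided worst cases. The article's only planning figure for loss is 10% attrition, and it does not place that in one arm. The calculation also covers binary endpoints only, whereas VAS percentage change, EQ-5D-5L and opioid change are not binary.

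Finally, the primary endpoint is tested in ITT with trial failures included and a multiple-imputation sensitivity analysis, and an unseen SAP may add support for the secondary endpoints. The first part stands. The second does not remove the point: the article does not leave the secondary population open but names it twice, and names a completer set.

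**Conclusion.** The point holds in a limited form. The article fixes a post-randomization completer set, mislabelled PP, as the population for all five ordered secondary superiority tests and the other non-primary comparisons, with no imputation stated for them. The status of SCS trial failures in that set is undetermined, because the withdrawal rule, the follow-up rule and the note on ITT do not settle it together.

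Bias cannot be excluded. It would favour SCS if trial failures are withdrawn, could run against SCS if dissatisfied CMM subjects leave, and is nil if loss is unrelated to outcome. For a binary endpoint under the assumptions above, one-sided loss of 10% moves the false-positive rate from 3.4% to between 5.1% and 7.6%, and 20% to between 8.4% and 21.4%. The shares lost and the response among the lost are assumptions, not figures from the article. The primary ITT conclusion is untouched.

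**What to change.** 1. Make ITT, as randomized, the primary population for the five secondary endpoints and for the between-group observational and healthcare-use comparisons.
2. State one missing-data method and apply it equally to both arms. For binary endpoints this could be multiple imputation that includes the trial outcome, or missing counted as non-response in both arms. For continuous endpoints it could be multiple imputation or a mixed model. A non-responder rule for SCS subjects alone would introduce its own asymmetry.
3. State that trial failures count in the SCS arm in these analyses.
4. Reconcile the withdrawal list in Methods, the 6-month follow-up statement in the SCS group section and the note in the analysis section, so that it is clear what 6-month data trial failures contribute.
5. Keep the present set, renamed completers, as a supportive analysis.

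The cost is revised wording and a little more analysis work; the secondary estimates may come out less favourable. No additional subjects are needed. The change should be documented before the secondary analyses are run.
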